### Outcome measures

The primary outcome of this study is changes in HbA1c levels pre and post intervention. Secondary outcome measures include changes in body weight, fasting blood glucose, blood pressure, quality of life and physical activity.

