#### Quantitative data analysis

Analysis of quantitative study data across randomised groups will be conducted in IBM SPSS version 20 (Armonk, NY). Continuous variables will be tested for normality and data, which are not normally distributed, will be analysed using Kruskal-Wallis and Wilcoxon signed ranks test. In the event of missing data, the last observation carry forward method will be used. A *p* value of < 0.05 will be considered as statistically significant for all the tests.

Effectiveness of the research intervention will be measured in terms of differences between study arms with respect to changes in biomedical measures and activities. Logistic regression will be used and both adjusted and unadjusted models will be presented. Benefits, barriers, confidence and knowledge will be included in a model to identify factors associated with the concept of intensive treatment and hypoglycaemia. An adjusted *t*-test using multiple linear regression analysis will be conducted to calculate variables for benefits, barriers and knowledge.

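### The effectiveness analysis names logistic regression for a continuous HbA1c change and defines no binary endpoint, so the named model does not estimate the mean difference the trial is powered on

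*Protocol article*

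**What the plan says.** The Outcome measures section states: "The primary outcome of this study is changes in HbA1c levels pre and post intervention". Table 1 also lists HbA1c as the primary variable. The Sample size calculation section gives 100 people per arm for 80% power to detect a 0.5-point HbA1c difference between arms.

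The Quantitative data analysis section then says four things that bear on how this outcome will be analysed:

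- The effect measure: "Effectiveness of the research intervention will be measured in terms of differences between study arms with respect to changes in biomedical measures and activities".
- The next sentence, and the only model attached to that statement: "Logistic regression will be used and both adjusted and unadjusted models will be presented".
- Continuous variables are tested for normality, and those that fail "will be analysed using Kruskal-Wallis and Wilcoxon signed ranks test".
- The only linear model is for other variables: "multiple linear regression analysis will be conducted to calculate variables for benefits, barriers and knowledge". A further model is meant to "identify factors associated with the concept of intensive treatment and hypoglycaemia".

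**The concern.** The outcome, the effect measure and the sample size all concern a continuous quantity compared between two arms. The model named for effectiveness handles a categorical outcome. No category is defined: the HbA1c limits of 7.5% and 11.0% under Sample recruitment procedures are entry criteria, not analysis thresholds.

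An analyst who follows the article has two choices. One is to pick a cut-off for HbA1c change after the fact, which loses power and leaves the threshold open to choice. The other is to set the stated model aside, in which case the article no longer fixes the primary analysis. Either way, the model named for effectiveness does not deliver the 0.5-point difference that justifies the sample size.

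**Working it through.** **1. Does any named method estimate the powered quantity?**

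| Named method | Compares arms? | Gives a mean HbA1c difference? |
|---|---|---|
| Logistic regression | Yes, on a binary outcome that is not defined | No, it gives an odds ratio |
| Kruskal-Wallis | Yes, but only for data judged non-normal | No |
| Wilcoxon signed ranks | No, it is paired within patient | No |
| Multiple linear regression | Assigned to benefits, barriers and knowledge | Not assigned to HbA1c |

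**2. Reproducing the plan's figure.** Inputs from the article: 100 per arm, 80% power, a 0.5-point difference, significance level 0.05. The article states neither an SD nor whether the test is two-sided. With a two-sided test and no clustering, the SD has to be back-solved:

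SD = 0.5 / [(1.960 + 0.842) × √(2/100)] = 1.262, so d = 0.5 / 1.262 = 0.396.

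The 100 per arm can therefore be matched only by assuming an SD of about 1.26. An SD of 1.25 needs 99 per arm, 1.3 needs 107 and 1.5 needs 142. With a one-sided test the implied SD would be 1.42.

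**3. Power if the change is dichotomised.** Keep the same normal shift, d = 0.396. If a proportion p_C of controls respond, the intervention proportion is p_T = Φ(Φ⁻¹(p_C) + 0.396). With p̄ the mean of the two proportions and n = 100 per arm,

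power = Φ{[(p_T − p_C) − 1.960 √(2p̄(1−p̄)/n)] / √[(p_C(1−p_C) + p_T(1−p_T))/n]}.

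| Control response | Intervention response | Power at 100 per arm | n per arm for 80% |
|---|---|---|---|
| 50% | 65.4% | 59.8% | 161 |
| 42.1% (median split) | 57.9% | 60.4% | 158 |
| 40% | 55.7% | 60.4% | 159 |
| 30% | 44.9% | 58.7% | 165 |
| 20% | 32.8% | 53.8% | 185 |
| 10% | 18.8% | 42.5% | 249 |

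The loss runs from 80 − 60.4 = 19.6 points to 80 − 42.5 = 37.5 points. In sample size, 158/100 to 249/100 is about 1.6 to 2.5 times as many patients.

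**4. The rank tests.** For normal data, Kruskal-Wallis with two groups has asymptotic efficiency 3/π relative to the t-test. The effective n is 100 × 3/π = 95.5 per arm, and the power is Φ{0.5 / [1.262 √(2/95.5)] − 1.960} = 78.2%. A simulation of 4,000 trials gave 76.6%, against 78.6% for the t-test. So this test costs about 2 points of power. The signed-rank test answers a different question. With an assumed fall of 0.3 or 0.5 points common to both arms, and so no arm effect, it was significant within a single arm in 64% or 97% of runs.

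**The case against.** The best defence is that a condensed article may leave the parametric method for normally distributed data to the full analysis plan, and that Kruskal-Wallis already compares arms on a continuous change with little loss. Both points are fair. Silence about the normal-data method is not a fault in itself. A reader might infer that the article has no valid between-arm comparison of HbA1c change, and Kruskal-Wallis shows that to be too strong. What remains is stated text: the model attached to effectiveness is logistic regression, and it does not fit the outcome.

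Other stronger readings are tempting and are not supported:

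- **Within-arm tests will serve as evidence of effect.** Patients enter with HbA1c of at least 7.5%, so regression to the mean could produce falls in both arms. But the article defines effectiveness as "differences between study arms with respect to changes in biomedical measures and activities". Nothing says that the signed-rank test will be used as proof of benefit.
- **Baseline is ignored.** The outcome is a change, and adjusted models are promised. Baseline adjustment in place of a change score is a gain in efficiency, not the correction of an error. With equal variances and correlation ρ, its residual variance is (1+ρ)/2 of the change-score variance: 0.65, 0.75 and 0.85 at assumed ρ of 0.3, 0.5 and 0.7.
- **There are few clinics.** The five centres belong to the exploratory phase. No number is stated for the main trial.
- **The factor models are the HbA1c analysis and use unmeasured variables.** They address a separate question: "Benefits, barriers, confidence and knowledge will be included in a model to identify factors associated with the concept of intensive treatment and hypoglycaemia". The Measurements section says that knowledge and self-efficacy are measured, and self-efficacy is close to confidence. Only benefits and barriers have no stated measure. For knowledge, only a named instrument is missing.

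**Conclusion.** The point holds in this form. The article defines effectiveness as a between-arm difference in change, powers it as a 0.5-point HbA1c difference, and then names a model that needs a binary outcome it never defines. That is a mis-stated primary method, not detail left for later. Kruskal-Wallis limits the harm only when the normality check fails, and even then gives no mean difference.

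The loss of power is conditional. If the change is dichotomised, power falls from 80% to about 54–60% at control response rates of 20–50%, and to about 42% at 10%. This rests on the back-solved SD of about 1.26, a two-sided 0.05 test, no clustering and hypothetical cut-offs. A reader might infer that the trial will certainly lose this power. The documents do not say so, because logistic regression implies a dichotomy but none is stated. The mismatch between model and outcome depends on none of these assumptions.

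**What to change.** - Make the primary analysis a linear mixed model of follow-up HbA1c on arm, with a clinic effect and baseline HbA1c as covariate. Report the adjusted mean difference with its 95% confidence interval.
- Stop using a normality pre-test to select the primary method.
- Keep logistic regression only for a binary secondary outcome whose definition and cut-off are named before the data are analysed.
- Minor: tie the exploratory models of benefits and barriers to variables that are collected, or delete them.

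The cost is wording in the analysis section. Table 1 already schedules HbA1c at visit 0, and clinic is the unit of randomisation, so no new data are needed. The change should be fixed before the final analysis.

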#### Qualitative data analysis

Focus group discussion will be transcribed verbatim and qualitative responses will be independently reviewed by the researchers (one psychologist, one pharmacist and one research assistant) to identify themes and develop a coding scheme.

### Cost-effective analysis

We will conduct a literature review to identify studies, which critically assessed the cost-effectiveness of an intervention in diabetes in this region. We will also collect data to examine healthcare resource use and indirect costs using standard economic analytical tools. Cost analysis using direct and indirect costs will be performed on the two study groups based on the number of referrals to specialists (e.g. endocrinologists, optometrists, podiatrist, dietitians), total clinic attendance and prescribed medications and tests linked to diabetes. The indirect costs will include travel cost, and cost such as days of sick leave from work and premature early retirement due to diabetes. The impact on quality of life will be assessed using EQ-5D scale by interviewing patients from the two groups before and after the intervention. This data will be used to estimate the cost/Quality Adjusted Life-Year (QALY) in cost utility analysis.

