### Articulation of study to HBM framework

Perceived barriers to self-care can hinder progress in patient participation. Several perceived barriers deter patient participation in regular SMBG. These include inconvenient programme days and time, lack of feedback, lack of reminders and the cost [25]. This study is designed to address these common barriers. To make participation convenient, follow-up sessions will be scheduled during participants’ regular appointments at the clinics. To address the barrier of time, diabetes classes will last for a maximum of one hour, screening and follow-up consultations will take approximately 1 h, while focus group sessions will last up to 2 h, will be conducted at separate sessions. Therefore, total contact time commitment for the entire programme will be seven and a half hours over a span of 1 year. To overcome the lack of feedback, participants in the telemonitoring group will receive an automated e-mail reminder if self-monitoring of blood glucose is not performed for three consecutive times while monthly follow-up calls to participants in the control group will be conducted. Furthermore, feedback will be provided to participants if blood glucose results show three continuous blood glucose values of ≤ 3.9 mmol/l or ≥11.1 mmol/l in the telemonitoring group. To overcome the cost barrier, the programme will be offered free to all participants.

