### Intervention arm

Participants in this arm will be encourage to self-monitor their blood glucose levels and will be provided with a group-based diabetes education, an automated feedback mechanism to both patient and family member(s) as well as an electronic logbook. The web-enabled function of the web-based glucose meter will be utilised, which when connected to an android enabled smartphone device, will automatically upload any blood glucose readings to an online portal which is currently managed by the Entra Health System. The web portal will host participant’s glycaemic and metabolic results as well as other information such as self-management skills, compliance to eye measurements and screening for microvascular complications. The system will be calibrated to generate a message to inform the attending doctor or researcher in the event that three consecutive readings of hypoglycaemia (3.9 mmol/L or below) or hyperglycaemia (11.1 mmol/L and above) are detected. A schematic diagram representing the elements of this system is shown in Fig. 2. The doctor or researcher will have the option to use this information to initiate an intervention. The doctor will be responsible for all treatment decisions. Participants in the intervention arm will receive monthly communications from the research team. Communications will focus on self-management skills, blood glucose control, and medication adherence. Figure 3 shows the process of the study trial.

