### Measurements

Table 1 details the measures that will be assessed throughout the study. HbA1c will be analysed using venous samples by ion-exchange high performance liquid chromatography (Cobas Integra 800, Roche), and serum lipids using enzymatic techniques (Advia 2400, Siemens). All blood specimens will be collected and analysed in a central laboratory operated by Gribbles Pathology, Malaysia to reduce variability.

**Table 1 Tab1:** Primary and secondary outcome measures for visit 0, 4, 12, 24, 52

Variable	Instrument
Primary outcome variable	
Glycaemic control	HbA1c
Secondary outcome variable	
Glycaemic control	Fasting plasma glucose
Blood lipids	Total cholesterol, LDL cholesterol, HDL cholesterol, triglycerides
Kidney function	Creatinine
Blood pressure	Measured twice using A&D UA-767 Plus BT-C blood pressure device on the same arm.
Blood oxygen saturation and pulse rate	Spo2; using Nonin Oximeter II Model 9560 on the right index finger.
Body Mass Index (BMI)	Calculated from height and weight measured by research staff.
Self-efficacy	Self-efficacy scale [46]
Diabetes distress	Diabetes distress scale [37]
Diabetes self-care	Diabetes self-care activities questionnaire [38]
Quality of life	EQ-5D [40]
Healthcare utilization	Self-reported using healthcare utilization questionnaire [39]
Smoking	Self-reported
Co-morbidities	Self-reported

*LDL* low density lipoprotein, *HDL* high density lipoprotein

Participants’ blood pressure will be calculated using the mean of two measurements performed with participants seated after at least 10 min rest, with the cuff on the predominant arm at the level of the heart (A&D, UA-767, USA). Body height and weight will be measured in light indoor clothing and without shoes using a stadiometer and a scale (A&D, UC-321 PBT-C, USA), respectively. Blood oxygen saturation and pulse rate will be measured using an oximeter (Nonin Oximeter II, Model 9560, USA).

Several generic and disease-specific instruments will be used in the current study to measure participants’ diabetes knowledge, quality of life, self-efficacy, diabetes distress and health care utilization. These include the diabetes distress scale [37], diabetes self-care activities [38], health care utilization [39] and EuroQol-5D (EQ-5D) [40]. Questionnaires will also be translated to Bahasa Malaysia and Mandarin if required, and subsequently validated.

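### The economic plan names no cost of delivering telemonitoring, and its QALY wording does not match the EQ-5D schedule in Table 1

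*Protocol article*

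**What the plan says.** **Costs.** The section Cost-effective analysis first sets out what will be collected: "We will also collect data to examine healthcare resource use and indirect costs using standard economic analytical tools". It then says the comparison of the two groups is "based on the number of referrals to specialists (e.g. endocrinologists, optometrists, podiatrist, dietitians), total clinic attendance and prescribed medications and tests linked to diabetes". On the other cost category it says: "The indirect costs will include travel cost, and cost such as days of sick leave from work and premature early retirement due to diabetes".

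**What the intervention arm receives.** Under Intervention arm, participants get "group-based diabetes education, an automated feedback mechanism to both patient and family member(s) as well as an electronic logbook". They also get a meter that, through a smartphone, "will automatically upload any blood glucose readings to an online portal which is currently managed by the Entra Health System". Three consecutive low or high readings send a message to the doctor or a researcher, and the research team contacts participants every month. The section Articulation of study to HBM framework adds monthly calls to the control group and states that "the programme will be offered free to all participants".

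**QALYs.** Cost-effective analysis says EQ-5D will be obtained by "interviewing patients from the two groups before and after the intervention" and that these data feed the cost per QALY. In Measurements, EQ-5D is a row of Table 1, whose title is "Primary and secondary outcome measures for visit 0, 4, 12, 24, 52".

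**Purpose.** The opening sentence of the Discussion makes the programme's cost-effectiveness one of the things the study is designed to assess. Relevance to public health addresses the results to policy makers.

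**The concern.** A cost-utility analysis of a programme has to charge the programme to the arm that receives it. Here the cost base covers what patients consume in ordinary care and what they lose in travel and work. The resources that distinguish the arms by design appear under no heading. Healthcare use is self-reported (Table 1) and the programme is free to participants, so patient questionnaires cannot recover the missing amount. Any saving in clinic use would then be credited to telemonitoring without the spending that produced it.

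On the effect side, the sentence that leads to the QALY mentions only a start and an end measurement, although the schedule offers five. If the analyst follows that sentence, three scheduled measurements are unused, and a gain that comes early, comes late or fades is misjudged. At stake is the figure a health system would use in deciding whether to pay for the programme.

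**Working it through.** The article states no unit cost, utility or cost per QALY, so there is no figure of its own to reproduce. The check has three parts.

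**1. Programme resources against the listed cost items**

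| Resource | Section | Matching cost item |
|---|---|---|
| Web-enabled meter and phone link | Intervention arm | None |
| Online portal, electronic logbook, automated feedback | Intervention arm | None |
| Group education | Intervention arm | None |
| Alerts to doctor or researcher | Intervention arm | None for the time spent; a resulting visit would count as clinic attendance |
| Monthly research-team contacts | Intervention arm | None |
| Monthly calls to control group | Articulation of study to HBM framework | None |

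**2. Effect of the omission on cost per QALY**

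Let D be the between-arm difference in the listed costs, C the net delivery cost per patient (intervention arm minus control-arm calls), and Q the QALY gain.

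- With delivery cost: (D + C)/Q
- As listed: D/Q
- Understatement: C/Q

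For positive C and Q the shift always favours telemonitoring, whatever D is. Neither C nor Q is in the article. Assumed values show the range:

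| Assumed C (RM) | Q = 0.01 | Q = 0.02 | Q = 0.04 |
|---|---|---|---|
| 300 | 30,000 | 15,000 | 7,500 |
| 1,000 | 100,000 | 50,000 | 25,000 |

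(RM per QALY; for example 300/0.02 = 15,000 and 1,000/0.02 = 50,000.)

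**3. Two EQ-5D points against five**

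Assumptions: Table 1 visits are weeks; the end measurement is week 52; the arms are equal at baseline; the largest utility difference is 0.05. The QALY gain is the trapezoidal area under the between-arm difference, divided by 52.

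| Course of the utility difference | Five visits | Weeks 0 and 52 only |
|---|---|---|
| Linear rise to 0.05 at week 52 | 0.05 × 26/52 = 0.025 | 0.05/2 = 0.025 |
| Linear rise to 0.05 at week 12, then held | 0.05 × (6 + 40)/52 = 0.0442 | 0.025 |
| 0.05 from week 12 to 24, linear fade to 0 at week 52 | 0.05 × (6 + 12 + 14)/52 = 0.0308 | 0 |
| Nothing until week 24, linear rise to 0.05 at week 52 | 0.05 × 14/52 = 0.0135 | 0.025 |

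Two points are exact in the first row. In the second they are 43% too low (1 − 0.025/0.0442), in the third they miss the whole gain, and in the fourth they are 86% too high (0.025/0.0135 = 1.86).

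The two problems need not act together. In the second row, two points would make cost per QALY 0.0442/0.025 = 1.77 times as high for the same positive incremental cost, which counts against telemonitoring, whereas the cost omission favours it.

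**The case against.** The best defence is that this is a condensed article. The cost section does not exclude delivery costs, does not call its list complete, and promises standard economic tools. Its list of indirect costs is openly illustrative. A full protocol or a health-economic plan may contain an intervention costing, and the costs could be taken from study records later. This stands as a limit on certainty. It does not remove the point: the article chose to itemise, the only illustrative wording in the direct-cost items concerns types of specialist, and the data it says it will collect are care use and indirect costs. Nothing shown points to delivery cost.

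On EQ-5D, the article uses similar start-and-end shorthand for HbA1c under Outcome measures, and Table 1 schedules HbA1c at the same five visits. The wording may therefore be loose rather than a chosen two-point method. The end point is also unclear: one section describes a year-long programme, and Relevance to public health mentions a 6-month follow-up. Both remarks are fair. If Table 1 is followed, the five-point data exist and only the wording needs repair.

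Three stronger readings are tempting and not supported:

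- A reader might infer that only downstream care is costed. Travel, sick leave and early retirement are also included.
- A reader might infer that EQ-5D is collected only twice. Table 1 lists it under five visits.
- A reader might infer that the cost per QALY is bound to be wrong, or that the programme is the largest cost difference between the arms. The first depends on the list being closed and, for QALYs, on the course of utility over time. The second needs cost figures that the article does not give.

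**Conclusion.** The point holds in two parts.

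**Cost.** The stated cost basis does not include what it costs to deliver the programme under evaluation. If the listed items are followed, cost per QALY is biased towards telemonitoring by C/Q. The direction is fixed once net delivery cost and QALY gain are both positive. The size cannot be determined from the article; the RM figures above are illustrations on assumed inputs.

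**QALY.** Cost-effective analysis and Table 1 do not agree on which EQ-5D measurements feed the QALY. A two-point calculation is correct under roughly linear change and can otherwise err in either direction. The sizes shown rest on an assumed 0.05 difference, on visits being weeks, and on the end measurement being week 52.

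The economic analysis is a stated objective but not the primary outcome, so the HbA1c comparison is untouched. The change should be made because it is cheap and the result is meant for policy makers.

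**What to change.** In Cost-effective analysis:

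1. Add programme delivery to direct costs, valued from study records: device, connectivity and portal, education sessions, staff time for monthly contacts and for handling alerts, and the staff time for any control-arm calls.
2. Replace the start-and-end wording for EQ-5D with a statement that QALYs are the area under the curve over all EQ-5D visits scheduled in Table 1, adjusted for baseline EQ-5D.

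The cost is a unit-cost list built from invoices and staff logs, plus two sentences of text. Staff time is best logged while the work is being done, and the Discussion schedules the end of data collection for December 2016. No visit or questionnaire is added if Table 1 is followed. The added costs will probably make the cost per QALY less favourable to telemonitoring; the change in QALY method could move it either way.
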